#### Settings

The seven participating Recovery Colleges linked to an NHS Trust with access to a CRIS system cover areas within five of the nine regions of England defined by the Office for National Statistics: South West, South East, East and North West England and London.

#### Measures

Work Package 3 will use the same primary and secondary outcome measures as for Work Package 2.

#### Procedures

Work Package 3 will run alongside Work Package 2. At the seven Recovery College sites involved in Work Package 3, participants will be asked if they would like to take part in Work Package 3 by consenting to data linkage using CRIS. Those that consent will comprise the intervention group for Work Package 3. This is outlined in Fig. 4 below. To identify the control group, propensity score matching [58] will be employed using the CRIS system at each site. This is a statistical matching technique that attempts to create a comparable control group for the Recovery College intervention group by accounting for the covariates, such as demographics and clinical history, that predict outcomes. Reverse anonymisation will be undertaken by CRIS staff and potential control participants will be contacted by NHS Trust staff working with CRIS staff to find out if participants are interested in hearing more about the study. Those that are will be provided with information sheets and will need to give informed consent to take part. The intervention group will complete those measures used in Work Package 2 and listed above at the same time points of baseline, 4, 8 and 12 months. The control group will complete the primary outcome measure and a restricted set of those measures used in Work Package 2 and the Work Package 3 intervention group, to reduce burden. Participants in Work Packages 2 and 3 will be compensated for their time completing assessments.

**Fig. 4 Fig4:**
[figure not shown]
Relationship between Work Packages 2 and 3 at Work Package 3 site

#### Analysis

We will compare the total MANSA score for service users who attended a Recovery College (intervention group) with those who did not (control group) at each follow up, controlling for baseline scores and hierarchical clustering of patients in Recovery Colleges. Specifically, we will fit a three-level random intercept linear regression model, considering observations from baseline, 4, 8 and 12 months at level 1, individuals at level 2 and Recovery Colleges at level 3. The model will include the MANSA scores at 4, 8 and 12 months as the outcome variables with intervention group, baseline MANSA score and sociodemographic characteristics, including the matching factors. A time x intervention interaction will be included to allow the effect to differ at each time point. Those secondary outcomes collected in both the intervention and control groups will be assessed similarly to the primary outcomes, using generalized linear mixed model (linear, logistic and Poisson depending on the distribution of the outcome.

Incremental economic analyses will be conducted from both a healthcare and a societal perspective with analyses conducted at 4, 8 and 12-month follow-up, controlling for baseline. Uncertainty will be addressed by generating cost-effectiveness planes from bootstrapped resamples. Cost effectiveness acceptability curves will examine the probability that the intervention is cost-effective for different decision-maker willingness-to-pay thresholds, as well as generating net benefit estimates. Sensitivity analysis will investigate key factors including the impact of costs of different Recovery College delivery models and the use of EQ-5D-5L/EQ-5D-3L cross-walk methods to generate utility [57]. The benefits of Recovery Colleges are likely to continue after the 12-month primary endpoint. Therefore, we will also carry out an economic evaluation informed by modelling to estimate longer-term benefits and NHS/Personal and Social Service and wider costs, using current design quality standards [59]. This requires an expert consensus panel to support model design, made up of Lived Experience Advisory Panel, Recovery College staff and the applicants, and representatives of Trusts and other affiliated organisations.

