#### Service use and economic benefits

There have been no formal economic evaluations of Recovery Colleges, and costing studies have focused on the impact on service use, rather than wider potential economic effects such as employment. Uncontrolled studies suggest that attendance is associated with reduced hospital and community service use [30, 31]. One such study found that Recovery College use was followed by a reduction in bed days, involuntary admissions, and community contacts over 18 months [30]. Reductions were greater for those students who had completed a course than those who had only registered. Authors estimated cost savings of UK£1,200 per registered student and UK£1,760 for students who completed a course. A further study suggested similar benefits [31]. A recent Australian costing study examined differences in costs of mental health community hours, mental health inpatient admissions and Emergency Department presentations that occurred before and after attending the Recovery College, in combination with top-down costs of the programme [32]. They reported overall net savings as A$269 per service user student per year in the 12 months post-enrolment, but also remarked on the challenges of comparisons across different funding arrangements for individual colleges.

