## Methods

### Design

The RECOLLECT programme comprises six work packages structured to relate to the RECOLLECT multilevel change model. Work Package 1 is a national survey of managers of Recovery Colleges in England, supplemented by qualitative interviews with a subsample of survey respondents. Work Package 2 is a prospective pre-post study of Recovery College fidelity and service user student outcomes and service use. Work Package 3 is a prospective controlled study comparing outcomes and service use among newly registered Recovery College service user students with a matched service user control group. Work Package 4 is a retrospective controlled study comparing routine clinical data for service user students with a matched control group. Work package 5 is a series of organisational case studies. Work Package 6 will mobilise the resulting knowledge from Work Packages 1 to 5. The inter-relationships and objectives addressed in Work Package 1 to 5 are shown in Fig. 3.

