#### Sample

To address Objective 3 we have conservatively assumed a small but clinically significant within-person effect size of 0.2 [41]. With standard deviation (SD) of 5 based on the mean difference of total score of the primary outcome measure, the Manchester Short Assessment (MANSA) [42] between baseline and follow up at 12 months with 95% power and 5% significance, assuming an intra-class correlation coefficient (ICC) of 0.02 [43, 44], an individual autocorrelation of MANSA score over time of 0.5 [45] and within-cluster standard deviation (SD) of 5, we require a sample size of 500. With an estimate of 20% attrition rate by 12 months, we will recruit 625 participants, for an analysable sample of 500. We will recruit 625 newly registering students (25 per college) who currently use secondary mental health services. Exclusion criteria will be insufficient knowledge of English to complete the outcome measures.

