#### Design and rationale

Work package 3 will employ a prospective controlled study design and include seven of the Recovery Colleges from Work Package 2, with which it will run in parallel. A non-randomised design will be employed due to the impossibility of individual level randomisation; most mental health service users have access to a Recovery College, even if not available in their Trust. The seven Recovery Colleges were selected for being linked to an NHS Trust which has access to a Clinical Record Interactive Search (CRIS) system, as this will be used to identify the control group.

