#### Sample

Intervention group eligibility will be as for Work Package 2; eligible controls will not be attending a Recovery College at baseline, or have previously attended a Recovery College. Work Package 3 will require approximately 48 students at each of the seven Recovery Colleges to form an intervention group of 330 participants; and 660 participants in total with the control group. This sample size is needed for 90% power to detect an effect size of 0.2 on the MANSA [46] using a two-sided test for the difference between two independent means and assuming α = 0.05. To meet this recruitment target, students at the seven Recovery College sites for Work Package 3 will be oversampled (i.e. 48 instead of 25 per site) relative to the others in Work Package 2.

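### Work Package 3 forms its groups by registration at baseline but words its primary comparison by attendance, which is known only later; the two should be reconciled

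*Protocol article*

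**What the plan says.** Four places set the groups by status at baseline.

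- Methods, Design: Work Package 3 compares outcomes "among newly registered Recovery College service user students with a matched service user control group".
- Work package 3, Sample: "Intervention group eligibility will be as for Work Package 2; eligible controls will not be attending a Recovery College at baseline". Controls must also have no earlier attendance.
- Work package 2, Sample, from which that eligibility is taken: "We will recruit 625 newly registering students (25 per college" and so on. The entry event is registration, and attending a course is not a condition.
- Work package 3, Procedures, on registrants asked for linkage consent at the seven sites: "Those that consent will comprise the intervention group for Work Package 3".

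Work package 3, Analysis, describes the comparison differently. The total MANSA score is compared for "service users who attended a Recovery College (intervention group) with those who did not (control group) at each follow up". The model that follows has an intervention-group term and a time by intervention interaction, with adjustment for baseline MANSA, sociodemographic characteristics and the matching factors.

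**The concern.** Registration and consent are known at baseline. Whether someone attended is known only afterwards. The propensity match is made on baseline covariates and can balance only the groups as recruited. If membership is then settled by later attendance, the groups compared are no longer those that were matched. The people who change place are likely to differ in motivation, early improvement or health. Adjusting for baseline MANSA and the matching factors does not remove differences that arise, or show themselves, after baseline.

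Both kinds of mismatch are foreseeable from the article. Some people register and go no further: the Background, under Service use and economic benefits, reports from an earlier uncontrolled study that "Reductions were greater for those students who had completed a course than those who had only registered". Controls can start attending, because Work package 3, Design and rationale, says that "most mental health service users have access to a Recovery College, even if not available in their Trust".

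At stake is the comparison that answers Objective 5 (Effectiveness) and on which Objective 6 (Cost-effectiveness) builds. Two analysts, one following the Analysis sentence and one following Design and Procedures, could place the same person differently.

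**Working it through.** **Step 1. The passages side by side.**

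| Person | Design, Sample and Procedures | Analysis sentence read literally |
|---|---|---|
| Registers, consents, attends | Intervention | Intervention |
| Registers, consents, never attends | Intervention | Not intervention (dropped, or counted with those who did not attend) |
| Control, never attends | Control | Control |
| Control, attends after baseline | Control | Not control |

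The two rules agree in rows 1 and 3 and differ in rows 2 and 4.

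**Step 2. Inputs for the size.** The article gives no figure for non-attendance, for controls who later attend, or for how non-attenders fare, so there is no figure of the plan's own to reproduce on this point. From the document: target effect 0.2 on the MANSA, and 330 per group (660 in total), from Work package 3, Sample. Assumed:

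- *a*, the share of registrants who never attend: 10 to 20%.
- *g*, how much worse never-attenders score than attenders for reasons unrelated to the college, in SD units and after the model's adjustment: 0.2 to 0.5.
- No true effect, and recruited groups perfectly matched with common mean M.

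**Step 3. Formulas.** Attenders then have mean M + *a g* and never-attenders M − (1 − *a*) *g*.

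- Never-attenders dropped: false benefit = *a g*.
- Never-attenders moved to an equal-sized control group: the control mean falls by (1 − *a*) *g* × *a*/(1 + *a*), so the false benefit = *a g* + *a*(1 − *a*) *g*/(1 + *a*) = 2*a g*/(1 + *a*).

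**Step 4. Results.**

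| *a* | *g* (SD) | Dropped: *a g* | Moved: 2*a g*/(1 + *a*) |
|---|---|---|---|
| 10% | 0.2 | 0.02 | 0.04/1.1 = 0.036 |
| 10% | 0.5 | 0.05 | 0.10/1.1 = 0.091 |
| 20% | 0.2 | 0.04 | 0.08/1.2 = 0.067 |
| 20% | 0.3 | 0.06 | 0.12/1.2 = 0.10 |
| 20% | 0.5 | 0.10 | 0.20/1.2 = 0.167 |

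The fourth row in head counts: 20% of 330 is 66 people. They lie 0.8 × 0.3 = 0.24 SD below the common mean. Moved to the controls, they make a group of 396 and lower its mean by 0.24 × 66/396 = 0.04. With the 0.06 gained in the intervention group, the total is 0.10 SD.

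Against the 0.2 target, the range runs from 0.02/0.2 = 10% to 0.167/0.2 = 83%. Controls who later attend are left out of this arithmetic. Their removal or transfer would add a further distortion whose size the article gives no means of judging.

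**The case against.** The strongest reply is that *attended* is loose wording for *registered*. The brackets in the Analysis sentence point back to an intervention group and a control group already fixed elsewhere, the model has no attendance variable, and no attendance-based analysis population is named. Work Package 4 mixes the terms in the same way: its Procedures take registration as the baseline date and then call the difference between the groups attendance. This reading is plausible and may well be what is meant.

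It does not settle the matter. The Background separates completing a course from merely registering. Control eligibility is stated in terms of attendance, so a person who has registered but not yet attended could, on the words alone, fit either group. The terms are not interchangeable in this design.

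A second reply is that handling of non-attendance and cross-over commonly sits in a full protocol or analysis plan that is not shown. That is right, and the absence of such detail is not the point. The point is a sentence that is present and disagrees with the recruitment rule.

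A reader might infer more than the article supports:

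- *That people will be reclassified or dropped.* Nothing says so.
- *That attendance is reassessed at every visit.* The reference to each follow-up says when MANSA is compared, not when membership is decided.
- *That attendance by controls goes unrecorded.* Work package 2, Measures, plans to record the number and types of courses attended. Controls complete a restricted set whose contents are not listed, so the item is neither shown to be kept nor shown to be missing.
- *That diluted effect and lost power belong to this flaw.* Dilution arises when people are kept in their recruited groups, which is the analysis recommended here. It also presumes that 0.2 is the effect among attenders, which the article does not state.

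**Conclusion.** The inconsistency is in the current text: recruitment is by registration and consent, and the primary comparison is worded by attendance. Whether it would do harm depends on which passage the analyst follows. If the Analysis sentence is only shorthand, nothing changes. If it is followed literally, group membership depends on behaviour after baseline and the propensity match no longer protects the comparison.

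Under the assumed ranges (10 to 20% never attending, outcomes 0.2 to 0.5 SD worse for other reasons, no true effect), the false benefit is about 0.02 to 0.17 SD against a 0.2 target. The lower end is negligible and the upper end is most of the target. The direction favours the college as long as never-attenders would have done worse anyway, which is likely but assumed. Because the sentence defines the effectiveness comparison and is nearly free to correct, it should be corrected before analysis.

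**What to change.** Reconcile Work package 3, Analysis, with Methods, Design, and with Work package 3, Sample and Procedures.

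1. In the comparison sentence, replace *attended* with *registered with*, and describe the controls as the matched group recruited at baseline.
2. Add one sentence: in the primary analysis every participant is analysed at all visits in the group to which they belonged at baseline, whatever their later attendance.
3. Label any analysis by actual attendance as secondary.
4. Confirm that the controls' restricted questionnaire set keeps the item on Recovery College courses attended that is already planned for Work Package 2, so that later attendance by controls can be reported.

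The cost is two sentences of wording and a check of the control questionnaire. The sample, the matching and the model stay as they are.

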### Work package 4: Retrospective controlled study of the effectiveness of Recovery Colleges

Work Package addresses Objective 7 (clinical data).

#### Design and rationale

Work Package 4 will employ a retrospective controlled study using routine clinical data and measures, with an 18 month follow up period. In comparison to Work Package 3, this study will benefit from a larger sample size and absence of selection bias in the intervention group, to produce results that will be more generalisable across NHS sites.

#### Measures

The Health of the Nation Outcomes Scale (HoNOS) [60] is a 12-item measure completed by clinical staff at all NHS mental health Trusts which covers a patient’s health and social functioning. Each item is scored on a five-point Likert scale. It has moderately high construct validity, fair to moderate test–retest reliability and good predictive validity [61].

DIALOG is an 11-item measure exploring health status and quality of life used routinely in many NHS mental health trusts, and based on the MANSA [62]. There are eight items on quality of life and three items on treatment, each scored on a seven-point Likert scale. Internal consistency is 0.71 for the eight quality of life measures and 0.57 for the three treatment items [62].

The Clinical Outcomes in Routine Evaluation – Outcome Measure (CORE-OM) [63] is a 34 item self-report measure covering subjective wellbeing, symptoms, function and risk used in many NHS mental health trusts. Each item is scored on a four-point Likert-scale. Internal consistency and test–retest reliability are good (0.75–0.95) [64].

#### Procedures

Five of the seven Recovery College sites used in Work Package 3 will be employed for this study (see Fig. 5), based on availability of student data and affiliation with an NHS Trust which has a CRIS. At each site service user student and CRIS data will be linked.

**Fig. 5 Fig5:**
[figure not shown]
Process for participant identification in Work Package 4

The intervention group will comprise all service user students who first registered at the Recovery College over 18 months prior to the selected audit date (the date of the data extraction from the Recovery College). Based on student numbers and the proportion who are service users we estimate 400 per site (total *n* = 2,000).

Individual service users in the control group will be matched with the students using a similar propensity scoring approach to that described in Work Package 3, so that as far as possible the only difference between groups will be Recovery College attendance. For the intervention group Recovery College registration will be used as the baseline date, and the last HoNOS and other available outcome scores recorded before Recovery College registration will be used as the baseline data. Eligible controls will also have a HoNOS score at the equivalent timepoint. The follow up HoNOS and other outcome scores to be used will be those entered as an update at the closest time point to the 18 month follow up point. For both groups, data on service use will be extracted for the 18 months after the baseline, including number of psychiatric inpatient days; number of contacts with staff in community mental health teams and specialist services such as psychology and outpatient services; and medications including doses prescribed.

#### Analysis

We will fit a two-level random intercept linear regression model, considering observations from individuals at level 1 and Recovery Colleges at level 2. We will compare HONOS scores of intervention group individuals at 18 months with 18-month HoNOS for matched control individuals adjusting for baseline HONOS and sociodemographic characteristics. The model will include 18 months HoNOS score as the outcome variable, and the baseline HoNOS score and sociodemographic characteristics as explanatory variables.

The relationship between Recovery College use, and mental health service use will be examined using both resource consumption parameters (categorical data) and derived individual-level costs (continuous data). Individual level costs will be calculated by combining service use data with appropriate unit costs, using the methods outlined in Work Package 1. Costs will be compared for the intervention group compared with matched controls using a bootstrapped regression model, adjusting for HoNOS and other outcome measures as available.

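### The Work Package 4 HoNOS model does not name the propensity-score matching factors as covariates, although the parallel Work Package 3 model does

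*Protocol article*

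**What the plan says.** The Work Package 4 Analysis section gives the covariates for the HoNOS comparison in two consecutive sentences. The first compares the students with "18-month HoNOS for matched control individuals adjusting for baseline HONOS and sociodemographic characteristics". The second lists the model terms and ends with "the baseline HoNOS score and sociodemographic characteristics as explanatory variables". Neither mentions the variables used for matching.

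The Work Package 3 Analysis section sets out the corresponding model for the MANSA with "intervention group, baseline MANSA score and sociodemographic characteristics, including the matching factors".

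The two studies find their controls in much the same way. Work Package 3 Procedures describes propensity score matching as "accounting for the covariates, such as demographics and clinical history, that predict outcomes". Work Package 4 Procedures matches controls "using a similar propensity scoring approach to that described in Work Package 3", with the aim "so that as far as possible the only difference between groups will be Recovery College attendance".

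**The concern.** These are two non-randomised comparisons in one programme, built on similar matching, yet their outcome models are described differently and no reason is given. The protocol itself presents clinical history as the kind of variable that predicts outcome. If such a variable is in the propensity score and matching leaves it somewhat unbalanced, a model containing only baseline HoNOS and sociodemographic characteristics does not remove what remains, apart from the part that baseline HoNOS captures.

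This matters more in Work Package 4 than in Work Package 3 because of sample size. Bias from a given imbalance does not shrink as numbers grow, but the standard error does. Work Package 4 is presented as the larger and more generalisable study, so a small leftover difference is more likely there to be read as an effect of Recovery College attendance.

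**Working it through.** **1. The plan's own figure.** Work Package 4 Procedures states five sites ("Five of the seven Recovery College sites used in Work Package 3 will be employed for this study") and an estimated 400 students per site: 5 × 400 = 2,000, which agrees with the stated total. The article gives no control ratio, effect size or power for this work package.

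**2. The covariate lists side by side.**

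| Term | Work Package 3 (MANSA) | Work Package 4 (HoNOS) |
|---|---|---|
| Group | named | not in the list, but clear from the preceding sentence |
| Baseline of the outcome | named | named |
| Sociodemographic characteristics | named | named |
| Matching factors | named | not named |

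**3. How much an omitted factor could matter.** The inputs below are assumptions, not figures from the protocol:

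- 1:1 matching, so n = 2,000 per group, with clustering and missing follow-up ignored;
- one matching factor with a standardised imbalance d of 0.05 to 0.20 remaining after matching and after the stated adjustment;
- a partial effect b of that factor on 18-month HoNOS of 0.1 to 0.3 residual SD per SD of the factor.

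Formulas: bias = d × b; SE = √(2/n) = √(2/2,000) = 0.0316 residual SD; with λ = bias/SE, the true two-sided error at nominal 5% is Φ(−1.96 − λ) + 1 − Φ(1.96 − λ).

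Worked case: d = 0.10 and b = 0.2 give a bias of 0.02, λ = 0.02/0.0316 = 0.63 and an error of 9.7%.

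Type I error at 2,000 per group:

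| d | b = 0.1 | b = 0.2 | b = 0.3 |
|---|---|---|---|
| 0.05 | 5.3% | 6.2% | 7.6% |
| 0.10 | 6.2% | 9.7% | 15.8% |
| 0.20 | 9.7% | 24.4% | 47.5% |

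The bias itself runs from 0.05 × 0.1 = 0.005 SD to 0.20 × 0.3 = 0.06 SD.

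**4. Sensitivity to the scale used.** Suppose effects are instead expressed in SDs of the outcome and a baseline-to-18-month correlation of 0.5 is assumed. Then SE = √(2/2,000 × (1 − 0.5²)) = 0.0274, and a bias of 0.02 SD gives 11.3% rather than 9.7%. The picture is the same.

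**5. Comparison with Work Package 3.** At 330 per group, SE = √(2/330) = 0.0778. With d = 0.10 and b = 0.3 (bias 0.03), the error would be 6.7%, against 15.8% at 2,000 per group. The study more exposed to leftover imbalance is the one with the shorter covariate list.

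**The case against.** The strongest case on the other side has four parts.

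- **The contrast may be one of wording.** The Work Package 3 sentence can be read as placing the matching factors inside the sociodemographic characteristics, and Work Package 4 uses that same term. A reader might infer that Work Package 3 expressly keeps clinical factors and Work Package 4 deliberately drops them. The documents do not support that. The Work Package 3 Analysis section never calls the matching factors clinical; the link comes from reading it with the Procedures section, where clinical history is only an example. The Work Package 4 matching set is described as similar and is not itemised. What stands is that the factors are named in one model and not in the other.
- **Much is already handled.** Matching deals with these variables at the design stage. Baseline HoNOS, a clinician-rated measure of health and social functioning and the baseline value of the outcome, is in the model. This stands, and it limits the residual problem without removing it, since balance is promised only as far as possible.
- **The sizes are assumed.** The protocol gives no residual imbalance, factor effect or matching ratio. Missing follow-up scores would raise the standard error and lower the inflation. This stands: the table is an illustration, and its lower end is negligible.
- **The article is condensed.** Fuller covariate lists often sit elsewhere. But the Work Package 4 covariates are not left open here: they are stated twice, and the same article did name the matching factors for Work Package 3.

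A reader might also infer that the group effect is missing from the Work Package 4 model because the list of terms omits it. The preceding sentence makes the comparison of students with matched controls plain, so this is no more than loose wording.

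**Conclusion.** The point holds as a minor one. As written, the Work Package 4 HoNOS model has a narrower stated adjustment than its sister analysis, despite similar matching, and no reason is given. Any residual imbalance in matching factors not captured by baseline HoNOS or sociodemographic characteristics would stay unadjusted.

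The size cannot be determined from the protocol. With one omitted factor, 1:1 matching, 2,000 per group and no clustering, the true type I error lies between about 5% and about 47% over the range examined, and the bias is at most 0.06 SD. It would be wrong to conclude that the Work Package 4 result will be biased, or that a significant difference there would be spurious: no post-match imbalance is reported, and good matching could make the effect negligible. The case for the change rests on consistency, and on the fact that it costs almost nothing in the study most sensitive to small imbalances.

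**What to change.** In the Work Package 4 Analysis section, list the terms of the HoNOS model as: intervention group, baseline HoNOS, sociodemographic characteristics, and the propensity-score matching factors, including any clinical history variables used in the score. This brings it into line with Work Package 3 and also puts the group term in the list.

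No new data are needed, because the variables must already be extracted from CRIS to do the matching. The only downside is a slightly larger model, which about 2,000 students can easily support. For a measured factor whose relation to outcome is correctly modelled as linear, the adjustment would return the error due to that factor to about 5%. It does nothing for unmeasured differences.

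### The Work Package 4 cost model does not say that its HoNOS and other score covariates are pre-registration values, and the stated service-use extraction provides no baseline cost to adjust for

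*Protocol article*

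**What the plan says.** All references are to the protocol article.

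- **Cost model** (Work package 4, Analysis): individual-level costs are compared between students and matched controls "using a bootstrapped regression model, adjusting for HoNOS and other outcome measures as available". No time point is attached to the scores, and no prior-use or baseline-cost term is named.
- **HoNOS model** (same section, preceding paragraph): this one is dated, "adjusting for baseline HONOS and sociodemographic characteristics".
- **Two sets of scores** (Work package 4, Procedures): for students, "the last HoNOS and other available outcome scores recorded before Recovery College registration will be used as the baseline data". The follow-up scores "will be those entered as an update at the closest time point to the 18 month follow up point".
- **Service use** (same section): "For both groups, data on service use will be extracted for the 18 months after the baseline". No earlier window is given.
- **Matching** (same section): controls are selected by a propensity approach similar to that of Work Package 3. The Work Package 3 Procedures give demographics and clinical history as examples of the matching covariates. Prior service use is neither named nor excluded.
- **Contrast** (Work package 3, Analysis): the incremental economic analyses there are adjusted for baseline.

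**The concern.** There are two separate weaknesses in the cost comparison.

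First, the covariates are described as outcome measures with no date. A HoNOS score recorded near 18 months may itself have been changed by attending the college. If it enters as a covariate, any saving that arises because students' health and functioning improved is adjusted away, and the coefficient no longer measures the total effect of attendance on cost.

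Second, earlier service use is a natural predictor of later cost, and registration may come at a particular point in a person's care. If students and controls differ in prior use after matching, and neither the matching nor the regression accounts for it, the difference carries into the cost comparison. The direction is unknown: heavier prior use among students would hide a saving, and lighter prior use would create or inflate one.

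The second weakness is a data decision as well as an analysis decision. If pre-baseline use is not extracted, no later analysis plan can adjust for it.

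**Working it through.** **1. The plan's own figure.** The only sample figure for this work package is 5 sites × 400 students = 2,000, which reproduces. It is not a power calculation and has no bearing on covariate choice.

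**2. Reading the passages together.** Procedures create a pre-registration score and an 18-month score for each person. The HoNOS model says which one is the covariate; the cost model does not. Both readings fit the words. The stated extraction starts at baseline, so a pre-baseline cost cannot be computed from it.

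**3. Effect of adjusting for 18-month scores (illustration).** The documents give no inputs, so these are assumptions in standard-deviation units: attendance changes 18-month HoNOS by a = −0.2; the direct effect on cost is d = −0.1; the slope of cost on 18-month HoNOS is b = 0.2, 0.4 or 0.6; prior use is balanced.

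Total effect = d + a·b. Once 18-month HoNOS is held fixed, only d remains. Share lost = a·b / (d + a·b).

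- b = 0.2: total −0.140; lost 0.04/0.14 = 29%
- b = 0.4: total −0.180; lost 0.08/0.18 = 44%
- b = 0.6: total −0.220; lost 0.12/0.22 = 55%

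A simulation of 400,000 records, adjusting for baseline and 18-month HoNOS, gave −0.104, −0.103 and −0.103, which are losses of 26%, 43% and 53%. Adjusting for baseline HoNOS alone gave −0.144, −0.184 and −0.220, so the benign reading is essentially unbiased.

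**4. Effect of a prior-use imbalance (illustration).** Further assumptions: the slope of cost on prior use is 0.5; baseline HoNOS = 0.3 × prior use + noise of SD 0.95; an imbalance of g SD remains after matching, with students the heavier users.

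Variance of baseline HoNOS = 0.09 + 0.9025 = 0.9925. The share of the imbalance absorbed by baseline HoNOS = 0.09/0.9925 = 0.091. Bias = 0.5 × g × (1 − 0.091) = 0.455g.

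- g = 0: bias 0
- g = 0.1: bias +0.045 (simulated +0.045 to +0.046)
- g = 0.2: bias +0.091 (simulated +0.088 to +0.093)

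Adding prior use to baseline HoNOS brought every simulated estimate to within 0.004 of the true total. Reversing the direction of the imbalance reverses the sign of the bias.

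**5. Precision.** If prior and later cost correlate at r, adjusting for prior cost alone cuts residual variance by r². For assumed r = 0.3, 0.5 and 0.7 this is 9%, 25% and 49%. Some of that gain would overlap with what HoNOS already explains.

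**The case against.** The strongest reply is that the benign reading is the natural one. Procedures use almost the same phrase about other available scores when defining the baseline data, and the model described just before the cost model names baseline HoNOS. A reader might infer that the plan does adjust for 18-month outcomes. The text does not say so, and on the baseline reading nothing is blocked. This stands: the fault is an ambiguity with one harmful reading.

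A reader might also infer that prior-use confounding is left in. That is not supported either. Controls are propensity-matched from clinical records, and clinical history could include earlier admissions and contacts. The extraction sentence describes follow-up data and does not define the matching variables, whose full list an article may leave to a longer document. This stands as far as it goes, but prior use is nowhere named and the cost model has no term for it.

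Three further inferences should be resisted:

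- The words about availability might suggest that patients or whole sites drop out, because DIALOG and CORE-OM are used in many Trusts and not all. No such exclusion is stated, and handling of partly recorded covariates can be left to an analysis plan.
- The description "using both resource consumption parameters (categorical data) and derived individual-level costs (continuous data" might suggest that days and contacts will be banded. Procedures collect them as numbers, and nothing says information will be discarded.
- The possible bias might be set against the savings quoted in the Background. Those come from an uncontrolled study, and the documents give no imbalance or correlation to scale by.

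Nor is this the only controlled look at service use, since Work Package 3 also compares it.

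**Conclusion.** The point holds as a cheap, worthwhile improvement and not as a demonstrated bias. Two facts are established from the text: the cost-model scores are undated although two dated sets exist, and the stated extraction yields no baseline cost, in contrast to Work Package 3.

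What follows is conditional. Part of the cost effect is removed only if 18-month scores are used; in the illustration the loss is roughly a quarter to just over a half, entirely on assumed pathways. Prior-use bias arises only if matching leaves an imbalance; it is zero if matching balances prior use. Neither size can be derived from the documents.

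**What to change.** - In the same CRIS extraction, also pull service use for a defined pre-baseline period, for example 18 months to mirror the follow-up.
- Include prior service use in the propensity model, and say so.
- Adjust the cost regression for pre-baseline cost and baseline HoNOS.
- State that every score used as a covariate is a pre-registration value (the equivalent time point for controls) and that no post-baseline outcome score is a covariate. Baseline DIALOG and CORE-OM need not be barred.

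If prior use is already among the matching variables, saying so meets the second item; the baseline-cost term is still worth adding for precision and for any imbalance that remains.

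Cost: a longer look-back in an extraction already planned, a few sentences of analysis text, and a rule for patients whose record history is shorter than the look-back.
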